## Abstract

**Introduction:**

Daily physiotherapy is believed to mitigate the progression of cystic fibrosis (CF) lung disease. However, physiotherapy airway clearance techniques (ACTs) are burdensome and the evidence guiding practice remains weak. This paper describes the protocol for Project Fizzyo, which uses innovative technology and analysis methods to remotely capture longitudinal daily data from physiotherapy treatments to measure adherence and prospectively evaluate associations with clinical outcomes.

**Methods and analysis:**

A cohort of 145 children and young people with CF aged 6–16 years were recruited. Each participant will record their usual physiotherapy sessions daily for 16 months, using remote monitoring sensors: (1) a bespoke ACT sensor, inserted into their usual ACT device and (2) a Fitbit Alta HR activity tracker. Real-time breath pressure during ACTs, and heart rate and daily step counts (Fitbit) are synced using specific software applications. An interrupted time-series design will facilitate evaluation of ACT interventions (feedback and ACT-driven gaming). Baseline, mid and endpoint assessments of spirometry, exercise capacity and quality of life and longitudinal clinical record data will also be collected.

This large dataset will be analysed in R using big data analytics approaches. Distinct ACT and physical activity adherence profiles will be identified, using cluster analysis to define groups of individuals based on measured characteristics and any relationships to clinical profiles assessed. Changes in adherence to physiotherapy over time or in relation to ACT interventions will be quantified and evaluated in relation to clinical outcomes.

**Ethics and dissemination:**

Ethical approval for this study (IRAS: 228625) was granted by the London-Brighton and Sussex NREC (18/LO/1038). Findings will be disseminated via peer-reviewed publications, at conferences and via CF clinical networks. The statistical code will be published in the Fizzyo GitHub repository and the dataset stored in the Great Ormond Street Hospital Digital Research Environment.

**Trial registration number:**

ISRCTN51624752; Pre-results.

Strengths and limitations of this studyThis research is directly related to four of the James Lind Alliance top 10 research priorities for cystic fibrosis; simplifying treatment burden, evidence for effectiveness of therapies to delay the onset of lung disease in early life, the application of new technology and exercise as a potential replacement for airway clearance techniques (ACTs).The longitudinal observational study design and novel use of daily remote monitoring captures detailed objective data from usual physiotherapy routine care and has the potential to provide real-world evidence to guide ACT practice where randomised controlled trials have failed.Variability in synchronisation or use of the ACT sensor and Fitbit or intermittent technical failure of either will make the analysis of remotely collected adherence data complex and challenging.Budget constraints, patient preference and the requirement to extract raw heart rate and step count data limited the choice of activity tracker which represented a potential compromise between data quality and willingness to wear the tracker.The development of a sustainable big data infrastructure including a pipeline for recording, syncing, processing and analysis of remote monitoring and clinical data was integral to this study and is vital for the future use of these technologies.

## Introduction

Cystic fibrosis (CF) is a life-limiting inherited condition, which affects over 10 000 people in the UK. Despite recent treatment advances, including modulator therapies that target the underlying cause of the disease,^1^ CF remains progressive and incurable. People with CF are susceptible to repeated respiratory infections due to thick respiratory mucus, which can lead to irreversible lung damage. Daily treatment to slow the progression of lung disease, and therefore the onset of respiratory failure, is the primary aim of almost all current CF therapies.^2^ Daily physiotherapy, including airway clearance techniques (ACTs), physical activity and exercise, is believed to mitigate the progression of CF lung disease.^3^

People with CF undertake a median of 10 different concurrent treatments that take an average of 2 hours each day.^4^ This high daily treatment burden (and high cost of care) from childhood has become a driver for research to maximise effective care and minimise unnecessary therapies. Reducing treatment burden has been identified as the top CF research priority by the James Lind Alliance.^5^ Follow-up research found that although ACTs were perceived as very important, they were considered the most burdensome daily treatment.^4^ ACTs are stressful for people with CF and their families, and adherence can be low. Of those questioned, 70% said they regularly missed some of their daily treatments, most commonly avoiding ACTs or nebulised therapies.^4^ Another study found those with the lowest adherence to chest physiotherapy had worse lung function, more exacerbations and consequently had higher health costs.^6^

Another of the James Lind Alliance top 10 research priorities for CF is to identify the specific therapies that could delay and prevent the progression of lung disease in early life.^5^ Despite over 70 years of ACTs in routine CF clinical practice, the evidence base to guide treatment remains weak. A number of challenges exist for researchers in the field; a plethora of physiotherapy ACTs and devices exist, providing a bewildering choice for therapists and patients, with the long-term effects of different devices, techniques or non-adherence being poorly understood. Traditional research methods (including randomised controlled trials) have failed to produce credible evidence for optimal ACT type, dose, frequency or duration.^7 8^ Established solitary outcome measures (eg, forced expiratory volume in 1 second; FEV_1_) are insensitive to change in mild CF lung disease, and are not useful endpoints for physiotherapy clinical trials. Furthermore blinding is not possible, patient or practitioner preferences can confound results of trials and ethical concerns about the complete removal of ACTs persist.^3^ There is evidence that patients with the lowest self-reported physical activity levels have poorer health,^9^ but the use of exercise as an ACT remains controversial,^10^ despite the fact it is popular with patients.^5^

Advances in technology, including increased use of electronically chipped devices, electronic patient records and the growth of big data analytics, are providing fresh opportunities for physiotherapy research. These may facilitate clarity and certainty about effective therapies and help to reduce treatment burden. Big data techniques, including machine learning and unsupervised clustering, are useful for analysis of healthcare data, which is often complex, unstructured and from multiple sources. However, they are yet to be used to build credible evidence to guide physiotherapy for people with CF.

### Project Fizzyo

This paper describes the protocol for Project Fizzyo, which uses innovative technology to capture detailed longitudinal data from children and young people with CF (CYPwCF) undertaking daily physiotherapy treatments. Real-time breath pressure during ACTs are captured daily, as well as heart rate and step count during physical activity. The interrupted time-series study design facilitates evaluation of interventions such as ACT feedback and ACT-driven gaming.

The aims of Project Fizzyo are (1) to monitor and understand adherence to daily ACT prescriptions, (2) to evaluate associations between ACT adherence and clinical outcomes under different study conditions (including feedback and gaming), (3) to monitor and understand daily patterns of physical activity in relation to published recommendations, and evaluate any associations with clinical outcomes and (4) to use big data analytics to seek out important data signals in relation to optimising ACT and exercise prescriptions for CYPwCF.

## Methods

### Study design

Project Fizzyo is an analytic longitudinal observational cohort study with an interrupted time-series design. Clinically prescribed ACT or exercise prescriptions for individual participants are continued as normal for the 16 months of the study. Each participant uses two remote monitoring sensors to record data daily. These are: (1) a bespoke Fizzyo ACT breath pressure sensor, inserted into their regular ACT device (Acapella Choice, Aerobika, AstraTech PEP or Pari PEP) and (2) a Fitbit Alta HR activity tracker (Fitbit, San Francisco, USA) to record daily physical activity (heart rate and step count). Participants synchronise (sync) data using software applications (apps) for each sensor, on a tablet computer provided for the study.

ACT feedback (daily number of breaths) and ACT-driven computer gaming are introduced and removed in an interrupted time series (figure 1), via the specially developed Fizzyo app. Baseline ACT patterns are recorded (during months 0–2: standard phase), then the sequential introduction of ACT feedback (during months 2–14: feedback phase) and ACT-driven gaming (during months 4–12: gaming phase) will allow any effect on breathing patterns, adherence or clinical outcomes to be observed. The removal of gaming (at month 12) and feedback (at month 14) will facilitate observation of lasting, temporary or feedback/game dependent behaviour changes.

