The number of children (recruitment period) at each hospital were: at GOSH 75 (10 September 2018 to 16 April 2019), RBH 40 (30 November 2018 to 31 May 2019) and RLH 30 (03 January 2019 to 01 July 2019). Data collection is ongoing and is predicted to end in December 2020.

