**Fitbit** Heart rate and step count	Removal of erroneous or non-physiological data (caused by improper wearing, depleted battery, full memory capacity due to infrequent syncing). Heart rate sampling frequency made consistent (per min) using a rolling average	Gaps in data Wear time (from heart rate data) Awake wear time Time in MVPA using personalised heart rate cut-off value^17^ Points crossing MVPA cut-off value	Heart rate Resting^20^ Peak Density and variability MVPA threshold switches Step count Daily step count Density and variability Active minutes (greater than a threshold value) Combined Active minutes both heart rate and step count. Step count during periods of MVPA	Daily time in MVPA compared with 60 daily minutes recommended. Weekly time in MVPA, 7 day window compared with 420 weekly minutes recommended.

Not all features shown.

*Features quantified as adherence per prescribed treatment session, per day, per rolling 7 day week, or other time point as required for analysis. ACT prescription is taken from clinical records and physiotherapy questionnaires.

†Total and/or average per treatment, SD, min, max values.

ACT, airway clearance technique; MPVA, moderate to vigorous physical activity.

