### Statistical analysis

The large amount of heterogeneous data to be recorded and collected for each participant will be analysed using R and visualised using R Shiny apps. Any changes in adherence to physiotherapy prescriptions or recommendations over time or in relation to ACT gaming or feedback, will be quantified. As CF phenotypes and physiotherapy adherence are complex and multifactorial, cluster analysis will define groups of individuals based on measured characteristics to identify subgroups of participants with distinct physical activity and/or ACT adherence profiles.

The Fitbit and ACT sensor dataset currently contains 50+ variables (key features shown in table 2), with more to be added from ongoing clinical record extraction. A correlation analysis of the features describing physiotherapy behaviours will remove features which are highly correlated. Variables with a Gaussian distribution will be normalised. Dimensionality reduction will be performed via principal component analysis. These methods will identify the most relevant and independent variables for cluster analysis to ensure a robust definition and visualisation of clusters.

Multiple features of ACT treatment sessions or activity days identified from the principal component and correlation analyses will be grouped using unsupervised cluster analysis, such that both the within-cluster similarity and between-cluster dissimilarity are strong. Unsupervised cluster analysis with the k-means method^18^ is a popular clustering technique and involves grouping multifactorial data into a pre-specified number of clusters. Numerous rapid computations comparing the relationship between multiple variables will determine the optimal cluster centres with the best separation between groups. The silhouette metric will be used to assess cluster homogeneity and separation, to identify the optimal number of clusters.

The associations, patterns and trends of individual physiotherapy adherence clusters to health outcomes (eg, lung function, number of hospital admissions, infections, antibiotics, etc) will be investigated with data from clinical records. Individual participant changes between clusters over time, or in relation to gaming or feedback, will also be investigated.

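### The gaming on/off contrast is confounded with season, because each child's gaming and non-gaming months fall in complementary parts of the year; calendar time should be in the model for the gaming effect

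*Protocol article*

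**What the plan says.** The Study design section of the protocol article sets one schedule for every child, with no concurrent control group:

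- "Baseline ACT patterns are recorded (during months 0–2: standard phase")
- "the sequential introduction of ACT feedback (during months 2–14: feedback phase")
- "ACT-driven gaming (during months 4–12: gaming phase")

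The inference drawn from taking the interventions away is: "The removal of gaming (at month 12) and feedback (at month 14) will facilitate observation of lasting, temporary or feedback/game dependent behaviour changes".

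Adherence to the airway clearance prescription in the different phases is a primary outcome (Adherence to physiotherapy). The Statistical analysis section says: "Any changes in adherence to physiotherapy prescriptions or recommendations over time or in relation to ACT gaming or feedback, will be quantified". It adds, at the level of the single child: "Individual participant changes between clusters over time, or in relation to gaming or feedback, will also be investigated". The article names no seasonal or calendar term.

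The Participants section gives the spread of entry: "at GOSH 75 (10 September 2018 to 16 April 2019), RBH 40 (30 November 2018 to 31 May 2019"), and 30 children at RLH from 3 January to 1 July 2019.

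**The concern.** The signature of a game-dependent behaviour is a change when games arrive at month 4 and a reversal when they go at month 12. Those two dates are eight months apart, and the non-gaming periods on either side are the same four months of the year. Anything in adherence that follows the calendar, such as infections, school terms or holidays, therefore gives the same rise-and-return pattern with no gaming effect at all. A linear trend in study time does not absorb a pattern that goes up and comes back.

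At stake is the gaming part of a primary outcome, and more sharply the reading of a single child's move between clusters against the gaming dates. Staggered entry cannot help at that level, because one child has only one entry date.

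**Working it through.** **Inputs.** The phase months come from Study design. Entry windows and site numbers come from Participants (75 + 40 + 30 = 145). Seasonal amplitude is not in the documents, so results are given per point and then over a range.

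**1. Position in the year.** Reduce study months modulo 12.

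- Gaming, months 4–12: positions 4 to 11.
- Non-gaming, months 0–4 and 12–16: positions 0 to 3, twice.
- Overlap: none.

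Checked day by day for all 295 possible entry dates (10 September 2018 to 1 July 2019), the overlap in day of year is at most one day, a month-end artefact. By *named* month, 285 of the 295 dates share two boundary months, because the phases switch mid-month.

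**2. Which contrasts are exposed.**

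- Game-dependent (months 4–12 against the rest): positions 4–11 against 0–3. Exposed.
- Lasting effect (months 12–16 against 0–4): positions 0–3 against 0–3. Season-matched.
- Feedback outside gaming (months 2–4 and 12–14 against 0–2 and 14–16): both sets cover positions 0–3. Season-matched.

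**3. Bias in one child's raw contrast.** Take a 12-month cosine of amplitude A. Its mean over L months centred at c is A · cos(2π(c − peak)/12) · sin(πL/12)/(πL/12).

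- Gaming: L = 8, centre at position 8, factor 0.866/2.094 = 0.4135.
- Non-gaming: L = 4, centre at position 2, factor 0.866/1.047 = 0.8270.
- The centres are six months apart, so the cosines have opposite signs and the worst-case difference is A × (0.4135 + 0.8270) = 1.24A.

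**4. Can gaming be estimated?** Regress the gaming indicator on child effects, linear trend, feedback and season, using monthly data, and take VIF = 1/(1 − R²).

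| Entry pattern | No season term | One annual harmonic | Twelve month effects |
|---|---|---|---|
| One child, or all entering in one month | 1.50 | 4.87 | not estimable (R² = 1) |
| Two adjacent entry months | 1.50 | 4.15 | 6.5 |
| Even entry, September–July | 1.50 | 1.51 | 1.51 |

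**5. Cohort bias with the stated site windows.** Entry dates were drawn uniformly within each site's window, or spaced evenly in it, with weekly data to month 16. The model had child effects, linear trend, feedback and gaming, and the worst peak date was taken.

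- Without calendar terms: about 0.5–0.65 point of bias per point of amplitude.
- With calendar-month terms: at most about 0.02 per point of amplitude (0.02 × 5 = 0.1 point for a 5-point season).
- Standard error for gaming: about 5–9% larger with calendar-month terms.

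**6. Range of amplitudes (assumed), by scaling steps 3 and 5.**

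| Amplitude, points | One child, raw contrast, up to | Cohort without calendar terms, up to about |
|---|---|---|
| 1 | 1.24 | 0.5–0.65 |
| 2 | 2.5 | 1.0–1.3 |
| 5 | 6.2 | 2.4–3.2 |
| 10 | 12.4 | 4.9–6.5 |

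**The case against.** The best reply is that the article states no model. It says changes will be quantified and nowhere excludes seasonal terms, and a condensed article leaves the covariate list to a fuller document. The dates needed are already collected. That stands as far as the silence goes: a missing covariate list is not an error. It does not dispose of the point. The inference that the article does state, reading the on/off pattern and individual cluster moves against the gaming dates, has no season-matched comparison within a child under the fixed schedule.

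Several stronger readings are tempting and are not supported:

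- *A child's gaming and non-gaming time never share a calendar month.* True by day of year within months 0–16, but most entry dates share two boundary months by name. The optional period after month 16, with games restored, lies outside this statement.
- *Gaming cannot be separated from season at all.* True within a child only for an unrestricted monthly season. A smooth harmonic, or an abrupt step at a dated switch as in an interrupted time series, identifies the effect under stronger assumptions. For the harmonic the price within one child is a VIF of 4.87 against 1.50.
- *The whole removal sentence fails.* The lasting-effect and feedback contrasts are season-matched.
- *Staggered entry already solves it.* Averaging the raw contrast over flat entry across the 9.7 months cuts the bias to 0.26 per point, but the stated site windows are uneven and overlapping. With them, about half of the 1.24 remains.
- *Rolling weekly scores inflate the type I error.* Table 2 lists "per rolling 7 day week" as one way to express a feature. No section proposes testing successive rolling values as independent, so no error rate follows.

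**Conclusion.** The point holds, limited to the game-dependent contrast and to individual cluster changes read against it. The complementary timing follows directly from the article's own schedule and needs no assumption. The size does need one: no seasonal amplitude is given, and the bias scales with whatever it is. The figures further assume a single annual cosine at its least favourable peak date and, for the cohort, uniform entry within each site's window. Real seasonality in adherence could be smaller, larger or differently shaped. If it were negligible, the bias would be too. It is worth acting on because the exposed contrast belongs to a primary outcome and the adjustment uses data already in hand.

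**What to change.** Estimate the gaming effect in one model across all children, with participant effects, a study-time slope, feedback and gaming terms, and calendar-month terms (eleven) or an annual harmonic (two). Entry from 10 September 2018 to 1 July 2019 makes these estimable. State that individual cluster changes at months 4 and 12 will not be attributed to gaming without this adjustment. Report the lasting-effect and feedback-outside-gaming contrasts separately, noting that they are season-matched by design.

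The cost is a standard error for gaming about 5–9% larger under the stated entry windows, and no new data collection. The harmonic uses fewer terms but assumes a smooth season. In the check it cost about the same precision as the monthly terms, so monthly terms are the safer default at cohort level.

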**Figure 1 F1:**
[figure not shown]
Study design flowchart of the 16-month study per participant. Participant assessment visits are in shaded boxes. ACTs and physical activity are recorded daily using electronically chipped devices (a bespoke ACT sensor and a Fitbit activity tracker). The specially developed Fizzyo app, as well as syncing ACT data throughout the 16 months, gives participant feedback in months 2–14 and ACT-driven gaming is available in months 4–12. ACT, airway clearance technique; CF, cystic fibrosis.

### Patient and public involvement

This study addresses top research priorities identified by people with CF, their families, carers and clinical teams as part of the James Lind Alliance CF Priority Setting Partnership.^4^ The ACT sensor and gaming were developed as part of the BBC2 programme, ‘The Big Life Fix’ at the request of a family with two sons who have CF.^11^ This idea was developed further by the study team, which includes a parent of children with CF, physiotherapy specialists and product design specialists. Children from Great Ormond Street Hospital (GOSH) and their families advised on the choice of Fitbit, development of the ACT sensor (including the addition of lights to indicate breathing), customisability of the Fizzyo app and games, the study design and information materials. Dissemination of study results to both participants in the study and the wider CF population is planned.

### Participants

To be eligible, participants at recruitment were: (1) aged 6–16 years, (2) diagnosed with CF and under the care of a participating London paediatric CF centre (either GOSH, the Royal London Hospital (RLH) or the Royal Brompton Hospital (RBH), including shared care patients) and (3) prescribed one of the four ACT devices compatible with the ACT sensor, at least once a day as part of routine ACTs.

Patients were excluded if (1) they/their parents did not or could not provide informed consent, (2) they were not prescribed one of the four specific ACT devices as part of their routine daily treatment (pre-study self-reported non-adherence to prescribed ACT did not prevent children from participation), (3) had undergone lung transplantation or (4) had a clinically significant medical condition other than CF.

Children meeting the eligibility criteria were approached by their clinical team with the study information sheets. Participant information sheets affirm that no direct benefits are promised to participants, although they may find the computer games help them to enjoy and engage with airway clearance. After 16 months the study will end for each participant and the ACT sensor and Fitbit will be returned. Participants can choose to keep the devices, with restored games and feedback for a short period at the end of their participation, on the condition that they continue to sync data until the remaining period of data collection is concluded for all participants (December 2020).

Participants were recruited from September 2018 to July 2019. The recruitment window was scheduled to be open for 6 months per site, though for the first and largest recruiting site (GOSH) an extra month was added to allow for a period of pilot data collection to resolve early technical issues. The initial recruitment target of 160 participants was reduced to 145 due to manufacturing delays for the bespoke Fizzyo sensor, which was not a threat to meeting the aims of the study. This study, with 145 CYPwCF is the largest CF population sample in any physiotherapy study undertaken in Europe to date. Daily data from these children over 16 months will provide sufficient precision of estimation in evaluating the signals of adherence to therapy.

The number of children (recruitment period) at each hospital were: at GOSH 75 (10 September 2018 to 16 April 2019), RBH 40 (30 November 2018 to 31 May 2019) and RLH 30 (03 January 2019 to 01 July 2019). Data collection is ongoing and is predicted to end in December 2020.

